**Figure 1 Fig1:**
[figure not shown]
**CONSORT flowchart for the SMART-PD trial.** CONSORT, Consolidated Standards of Reporting Trials; OP, Outpatient; PTA, Parkinson’s tracker app; SMART-PD, Smartphone- and internet-assisted self-management and adherence tools to manage Parkinson’s disease; TAU, Treatment as usual.

### Sample size

The sample size for the smartphone- and internet-assisted self-management and adherence tools to manage Parkinson’s disease (SMART-PD) trial has been determined in a pragmatic manner based on available funding to demonstrate both the effectiveness and the ease of implementation of the intervention. The sample size was calculated along two dimensions: the primary outcome (that is, MMAS-8 score) and the secondary outcome (QoL). The main sample size calculation was based on the primary endpoint. To detect a 1-point improvement on the MMAS-8 with a standard deviation (SD) of 2.5 and 80% power at the 5% significance level would require 200 subjects (100 in each group, 1:1 allocation). To allow for 10% loss due to dropouts and those lost to follow-up, we would need to recruit 222 subjects (111 in each group, 1:1 allocation). The study is also powered to detect a 6-unit difference in the secondary outcome, QoL (PDQ-39). With a SD of 9 and 80% power at the 5% significance level, 74 subjects would be required (37 in each group, 1:1 allocation). To allow for 10% loss due to dropouts and those lost to follow-up, we would need to recruit 82 subjects (41 in each group, 1:1 allocation). Therefore, 222 participants will be recruited.

### Intervention group

#### Parkinson’s tracker app

Participants allocated to receive the intervention will receive instructions to download the PTA to their Android or iPhone smartphones or tablet devices or to access it via a website portal within 1 day after they have attended their outpatient appointment. The app consists primarily of the following features:

•Using a sliding petal interface (Figure 2), participants will adjust their daily scores on eight to ten self-monitoring measures on a 5-point scale: water, sleep, exercise, 5 A DAY healthy diet, mood and energy, medication, movement, suppleness and control. Participants who have difficulty manipulating the flower icon due to their motor symptoms will have the option of using an accessibility mode with a zoom function to magnify the screen. Participants will be able to review their scores and compare ‘petals’ against each other.

**Figure 2 Fig2:**
[figure not shown]
**Screenshot of the self-tracking interface.**A reminder system for patients to receive alerts and track medication intakeAn option to generate a compiled report of data entered by the patient over the trial period that will serve as an aid for shared decision-making during their follow-up outpatient appointmentGames to track physical responsiveness (finger-tapping task) (Figure 3) and cognition (number-size Stroop test) (Figure 4)

**Figure 3 Fig3:**
[figure not shown]
**Screenshots of the finger-tapping test.**

**Figure 4 Fig4:**
[figure not shown]
**Screenshots of the number-size Stroop test.**

##### Finger-tapping test

In the finger-tapping test, participants have to tap the screen of the smartphone as many times as they can in a 20-second period, alternating between two circular targets. The game displays the participant’s cumulative score. The app also records variations in responses.

##### Number-size Stroop test

In the number-size Stroop test, the game displays two circular targets, each containing a number in the range 1 to 99 in various font sizes. Participants have to tap the *numerically* larger value and visual size information. Participants get points for correct answers when they select the numerically larger number. The game lasts 20 seconds and displays the cumulative score. The app also records reaction times and variability in responses.

#### Tracking progress

Clinicians will have access to a dedicated web portal where they can see participants’ progress over the trial period. Participants will also have access to a dedicated web portal. However, neither group will be able make changes to any data. At the follow-up appointment, participants in the PTA group will be able to generate a report compiled from the data they have entered over the trial period to share with their clinicians (see Figure 5).

**Figure 5 Fig5:**
[figure not shown]
**Screenshot of a sample report generated by the Parkinson’s tracker app.**

### Treatment-as-usual group

They will have their regular OP clinical assessments, including symptom review followed by a medication review, at the start of the trial and at the end of 16 weeks. We do not expect any adverse events to occur during the trial.

### Statistical analysis

The trial statistician will be blinded to the allocation of trial participants. In the main analysis, the effect of the interventions on the primary and secondary outcomes will be assessed. The generalised linear model (GLM) will be employed for analysis of the primary endpoint (MMAS-8 at 16 weeks). The GLM model will have treatment as the fixed effect and baseline measurement of the primary endpoint as the covariate. For GLM model analysis, normal distributions will be used in the GLM, and the mean difference in MMAS-8 with its 95% confidence interval will be derived and reported. Model assumptions about residuals in regression analysis will be checked by inspection of residuals versus a fitted values plot. In addition, adjusted analysis and subgroup analysis with prespecified covariates will be performed on the primary endpoint analysis.

For the secondary outcomes (QoL, depression, anxiety, nonmotor symptoms, and degrees of depression and anxiety), the analyses will be performed in an analogous fashion within the framework of GLM. In addition, summary statistics will be generated for the primary and secondary endpoints with number (%) expressed for binary outcomes and number, mean and SD used for continuous outcomes.

Analysis of the primary and secondary outcomes will be carried out in adherence to the intention-to-treat principle (that is, the participants will remain in the group to which they were randomised and not analysed according to the interventions actually received). In addition, supplemental per-protocol analyses will be performed. Detailed results of statistical analysis will be described in the statistical analysis plan, which will be finalised before lockup of the database. The SAS 9.2 statistical software package (SAS Institute, Cary, NC, USA) will be used for all the data analyses.

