**Methods/Design:**

A 4-month multicentre RCT with 222 patients will be conducted to compare use of a smartphone- and internet-enabled Parkinson’s tracker smartphone app with treatment as usual for patients with PD and/or their carers. The study investigators will compare the two groups immediately after intervention. Seven centres across England (6) and Scotland (1) will be involved. The primary objective of this trial is to assess whether patients with PD who use the app show improved medication adherence compared to those receiving treatment as usual alone. The secondary objectives are to investigate whether patients who receive the app and those who receive treatment as usual differ in terms of quality of life, quality of clinical consultation, overall disease state and activities of daily living. We also aim to investigate the experience of those receiving the intervention by conducting qualitative interviews with a sample of participants and clinicians, which will be administered by independent researchers.

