### Outcome measures

The primary outcome measure is adherence to treatment as determined by Morisky Medication Adherence Scale (MMAS-8) score at 16 weeks [36, 37]. The response categories are ‘yes’ or ‘no’ for each item with a dichotomous response and a 5-point Likert response for the last item. A ‘yes’ response is scored as 1 and a ‘no’ has no score. The primary endpoint will be the total MMAS-8 score at 16 weeks. We are collecting data from a range of secondary outcome measures, including the following:

Parkinson’s Disease Questionnaire (PDQ-39) to measure QoL [38]Quality of consultation for PD patients (from the *Patient-Centered Questionnaire for PD*[39]Non-Motor Symptoms Scale [40]Hospital Anxiety and Depression Scale [41]Beliefs about Medication Questionnaire [42]

In addition to the measures listed above, we will collect demographic data at baseline, such as participant age, duration and severity of PD (Unified Parkinson’s Disease Rating Scale score if recorded in clinical file), medication profile (types of medication, dosage level and frequency), socioeconomic status, ethnicity, comorbidities, level of education and whether medication is self-administered or given by a spouse or carer. We also will collect patients’ self-reported ratings and game scores within the application.

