### Randomisation and masking

Eligible patients for whom consent or assent is provided will be allocated in a 1:1 ratio to the two arms of the study according to a computer-generated random sequence stratified by centre and using blocks of variable size. The allocation sequence will be generated by the trial statistician and will not be available to any member of the research team until databases have been completed and locked. In view of the established safety record of study interventions, there will be no provision for emergency unblinding of participants, and copies of the allocation sequence will not be held at the recruiting centres.

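### Randomisation is stratified by centre, but the primary model leaves centre out; the result is a mildly conservative analysis if centres differ, and the fix is nearly free

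*Protocol article*

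**What the plan says.** Under Randomisation and masking, the protocol article says that patients "will be allocated in a 1:1 ratio to the two arms of the study" by a "computer-generated random sequence stratified by centre and using blocks of variable size". The abstract gives the number of strata: "Seven centres across England (6) and Scotland (1) will be involved".

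Under Outcome measures, "The primary endpoint will be the total MMAS-8 score at 16 weeks". Under Statistical analysis, the model for that endpoint is written out: "The GLM model will have treatment as the fixed effect and baseline measurement of the primary endpoint as the covariate". The reported result comes from the same model: "normal distributions will be used in the GLM, and the mean difference in MMAS-8 with its 95% confidence interval will be derived and reported". The secondary outcomes are to be handled analogously within the same model framework.

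A further sentence reads "In addition, adjusted analysis and subgroup analysis with prespecified covariates will be performed on the primary endpoint analysis". It does not name the covariates. The article gives no reason for leaving centre out of the main model.

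**The concern.** Blocking within centre makes the two arms nearly equal in size at every centre. Differences between centres in the outcome then largely cancel out of the treatment comparison, so the true sampling variance of the estimate contains little of them. A normal model without a centre term cannot see this. It counts the between-centre variance as residual noise, and its standard error is larger than the design warrants.

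What is at stake is precision. The sample size was set pragmatically within the available funding and for 80% power, so recruiting more patients is not an easy way to regain precision that the analysis gives away.

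**Working it through.** **The plan's own figure.** Input: "To detect a 1-point improvement on the MMAS-8 with a standard deviation (SD) of 2.5 and 80% power at the 5% significance level". Two-sided, n per arm = 2 × (1.960 + 0.842)² × 2.5² / 1² = 98.1, so 99; the t-test version gives 100 per arm, 200 in all. Then 200 / 0.90 = 222.2, stated as 222. The figure reproduces and is not in dispute. It uses neither baseline nor centre.

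**Inputs for the check.** From the article: seven centres, 1:1 within centre, SD 2.5 (variance 6.25), a 1-point effect. Assumed, because the article gives neither: correlation 0.5 between baseline and 16-week score within centre, and an ICC from 0 to 0.20, defined as the between-centre share of total variance. Take 7 × 28 = 196 evaluable patients, close to the planned 200.

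**Formulae.** With equal arms, SE = √(R × 4/196) = √R / 7, where R is the residual variance, and interval width = 2 × t × √R / 7. Residual degrees of freedom are 196 − 3 = 193 without centre (t = 1.972) and 196 − 9 = 187 with centre (t = 1.973).

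- Within-centre variance: Vw = 6.25 × (1 − ICC).
- Expected variance of seven centre effects about their own mean: Vu = 6.25 × ICC × 6/7.
- Centre in the model: R = 0.75 × Vw.
- Centre omitted, effect at follow-up only: R = 0.75 × Vw + Vu.
- Centre omitted, same effect at baseline and follow-up: R = (Vu + Vw) − (Vu + 0.5 Vw)² / (Vu + Vw). The baseline covariate absorbs much of the centre effect.

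**Worked case, ICC 0.20.** Vw = 5.000 and Vu = 1.071.

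- With centre: R = 3.750, width 2 × 1.973 × 1.936 / 7 = 1.091.
- Without, follow-up only: R = 4.821, width 2 × 1.972 × 2.196 / 7 = 1.237, which is 13% wider.
- Without, both times: R = 6.071 − 3.571² / 6.071 = 3.97, width 2 × 1.972 × 1.993 / 7 = 1.123, which is 3% wider.

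| ICC | Width with centre | Without, effect at follow-up only | Without, effect at both times |
|---|---|---|---|
| 0 | 1.220 | 1.220 (0%) | 1.220 (0%) |
| 0.05 | 1.189 | 1.224 (+2.9%) | 1.198 (+0.7%) |
| 0.10 | 1.158 | 1.229 (+6.1%) | 1.174 (+1.4%) |
| 0.20 | 1.091 | 1.237 (+13.4%) | 1.123 (+2.9%) |

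**Power and type I error by simulation** (same set-up, exact 1:1 within centre; without versus with centre):

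- Follow-up only (2,000 trials per setting): at ICC 0.20, power 91% versus 95%. The actual type I error without centre is about 3.3% at ICC 0.20 and about 4.2% at ICC 0.05.
- Both times (4,000 trials per setting): power 90.2% versus 90.5% at ICC 0.05, 92.3% versus 92.6% at 0.10, and 94.4% versus 94.9% at 0.20. Type I error at ICC 0.20 is 4.4% versus 4.8%.

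**Cost when centres do not differ.** With N = 200, blocks of 2, 4 and 6, and no baseline correlation, simulated power at ICC 0 is 80.3% without centre and 80.2% with it.

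**The case against.** The strongest reply is that this is harmless. Any error is in the safe direction, and baseline adjustment already removes much of any lasting difference between centres. Under the assumed baseline correlation of 0.5, power without centre is about 90%, above the planned 80%. All of that stands, and it limits the point to lost precision.

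A second reply is that the adjusted analysis may include centre, or that the analysis plan, which is not shown, may add it. Either is possible. But the article introduces the adjusted analysis as an addition and does not name its covariates, so it does not replace the model that gives the primary answer. The article could have left the model terms to the analysis plan; instead it states them. This is therefore a stated choice and not a detail lost in condensing.

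A reader might also infer more than the documents support:

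- *That the trial would produce false positives or a biased estimate.* Ignoring a balanced stratification factor in a normal linear model works the other way.
- *That the loss of precision is a fact.* It is conditional: with no centre differences it is nil, and the article does not quantify them.
- *That the 13% figure is what to expect.* It needs both the highest ICC in the range and a centre effect that is absent at baseline. A stable difference in case mix would appear at both times, and the loss is then about a quarter of that or less.
- *That the sample size is wrong.* It reproduces.

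**Conclusion.** The mismatch between design and model is real and plainly stated in the article. Its effect is conservative and of unknown, probably modest, size. Over ICC 0 to 0.20 the interval is 0% to about 3% wider than needed if centre differences are the same at baseline and follow-up, with a power loss of about one point or less. If they arise only by follow-up, it is 0% to about 13% wider, with a power loss of up to about 4 points. These ranges rest on the assumed ICC, the assumed baseline correlation of 0.5 and equal centre sizes, none of which the article gives. No planned conclusion is put at risk. The point is worth acting on because the correction costs almost nothing.

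**What to change.** Before database lock, change the model sentence under Statistical analysis so that the primary model has treatment and centre (the stratification factor), with baseline MMAS-8 as covariate. Centre may be a fixed effect with seven levels or a random effect; either serves, and the choice should be stated in advance. Use the same structure for each secondary outcome, with that outcome's own baseline as covariate.

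The cost is one sentence and at most six of about 193 residual degrees of freedom. No change to the sample size, randomisation or data collection is needed.

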### Exploratory analyses

Self-reported scores and game data from the PTA provide an opportunity to perform exploratory analysis of patterns of day-to-day variation and correlation of Parkinson’s symptoms with medication intake and other health behaviours. Previous researchers have found that daily self-tracking and data from the finger-tapping test give a detailed and sometimes conflicting picture of a patient’s condition compared to retrospective self-assessment [45]. Data recorded daily within the PTA will be used to examine correlations between various items collected via the PTA at individual and group levels. These scores will also be used in regression analyses against the primary and secondary outcome measures.

### Qualitative evaluation

Semistructured interviews will be undertaken by an independent agency with a purposively selected subsample of participants (*n* ≤ 5) to explore the process and experience of using the PTA. We will interview only participants who consent to be interviewed. All participants who give us consent will be pooled, and those who will be interviewed will be selected at random to minimize selection bias. Interviews will be 45 minutes in duration. The aims are to complement the quantitative findings by obtaining insights into the experience of using the PTA, consider which elements of the PTA are most helpful, explore perceptions of how the PTA has influenced medication taking and explore how the PTA could be improved. Exploratory correlational analysis will be performed on the self-report and game score data collected by using the PTA.

### Ethical considerations

We do not anticipate any serious risk to trial participants, as we assume that patients will take their medications as prescribed by their clinicians. However, there is a possibility that increased medication adherence in PD may lead to a greater incidence of medication induced side effects, such as dyskinesia, postural hypotension, confusion, nausea and impulsive and/or compulsive behaviour disorders resulting from dopaminergic therapy for PD. We will alert patients about these potential side effects in the Patient Information Sheet and advise them to contact their clinical team, if necessary, as part of routine clinical practice.

### Trial monitoring

We will assess the impact of using self-management tools delivered via smartphones and the web, along with routine treatment, for 16 weeks. The trial protocol has minimal to no risk of worsening PD progression. These factors led us to form a monitoring group rather than a Data Monitoring Committee. Monitoring of the trial will be performed by the Trial Management Group (TMG), which will consist of lead investigators from each site and the Chief Investigator (CI) from uMotif. The CI will call and/or email each trial site every 2 weeks to check if there have been any issues with software and to follow up on recruitment rates. The CI will send a monthly update to each of the trial sites and to the NHS research and development lead. The trial advisory board will include members of the TMG and representatives from The Cure Parkinson’s Trust UK and Parkinson’s UK. It will be chaired by [name] from The Cure Parkinson’s Trust. We have scheduled three TMG meetings—one prior to the start of the trial, one midway through and one at the end of the trial. Any issues related to the software, participants or the trial, including protocol amendments, will be discussed and resolved by the TMG at the meeting scheduled for midway through the trial.

### Trial administration

Administration of the trial reflects the allocation of responsibilities set out in the Research Governance Framework [46]. The CI will be in charge of conducting the trial according to the agreed protocol and in accordance with legal requirements, guidance and accepted standards of good practice; will arrange to make findings and data accessible following expert review; and inform participants of the research results. Lead investigators at the trial sites will conduct the trial according to the agreed protocol and in accordance with legal requirements, guidance and accepted standards of good practice; will ensure participants’ welfare while in the study; and will arrange to make findings and data accessible following expert review. The trial sponsor is responsible for establishing and keeping in place arrangements to initiate, manage and fund the study.

### Data management

Data will be stored securely on hardened servers and backed up. To maintain data protection, the sponsor has notified the Information Commissioner’s Office that it is a data controller and processor. No data will be shared with anyone or any entity other than the trial team. Data sets will be anonymised before transfer to the outcomes assessor (that is, the trial statistician) at the end of the trial. The trial statistician and sponsor will have access to the final data set.

### Publication policy

#### Reporting and dissemination

Prior to submission or application for presentation, all manuscripts, posters, oral presentations and other reports of the outcomes of this research effort will be approved uMotif. All publications will include a formal acknowledgement that the trial was designed by uMotif with feedback from trial sites, and the Liverpool School of Tropical Medicine and that it was or is being carried out by uMotif and all trial sites. We will also acknowledge that the trial was supported by The Cure Parkinson’s Trust and Parkinson’s UK and that the study was commissioned by NHS Midlands and East and funded by the UK Department of Health.

#### Authorship

The authorship of manuscripts, posters, oral presentations and any other reports of the results of this study will be guided by the criteria for authorship formulated by the International Committee of Medical Journal Editors as published in its *Recommendations for the Conduct, Reporting, Editing, and Publication of Scholarly Work in Medical Journals*[47]. According to these requirements, the authors should meet the following criteria: (1) Each author should have participated sufficiently in the work to take public responsibility for the content; and (2) authorship credit should be based only on substantial contributions (a) to the conception and design or analysis and interpretation of data; (b) to the drafting of the manuscript or to revising it critically for important intellectual content; and (c) by giving final approval of the version to be published. Conditions 2a), 2b) and 2c must be met. A plain English summary of the findings will be sent to all trial participants.

